### Sample size and statistical analysis

This study is purely exploratory and aims to evaluate safety and tolerability of PBI-4050 and examine its effects on biomarkers. The study will collect data to derive descriptive statistics on secondary endpoints for future studies and no statistical hypothesis will be tested. A minimum of 8 subjects is deemed necessary in this part of the study. The data will be summarized using mean, standard deviation, median, and range. Demographic (sex, age, race, ethnicity, waist circumference, height, weight, and BMI) and baseline characteristics will be presented descriptively at baseline. Categorical variables will be reported as numbers and percentages. Paired t-test or where appropriate the non-parametric equivalent (Wilcoxon signed-rank test) will be used to compare variables before and after intervention. The Shapiro-Wilk test will be used to test the normality of the distribution. In the event that the normality assumption fails at the 0.10 alpha level of significance, the Wilcoxon Signed-Rank test will be used instead. Absolute values and changes from baseline in safety laboratory tests will be summarized by visit over time and presented in shift tables. To evaluate the shift over time, a mixed model comparing the slope before baseline (historical data) to the slope after baseline (on-treatment data) will be used. For comparing results of repeated samples, for example adipose tissue microdialysis where there are multiple time points during the same test, repeated measures analysis of variance will be used. All analysis will be conducted using SPSS statistical software. The significance level for this study is set at *p* < 0.05. All statistical analyses will be made using observed data. No imputation will be made.

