## Background

Alström syndrome (ALMS) is a rare autosomal recessive genetic disorder with an estimated prevalence of less than one per million [1]. It is characterized by retinal cone-rod dystrophy, hearing loss, childhood obesity, hyperinsulinemia, severe insulin resistance, as well as type 2 diabetes mellitus (T2DM), hypertriglyceridemia and multiple organ dysfunctions due to progressive fibrosis. Increasing systemic fibrosis develops as patients age, with clinical manifestations in multiple organs. The severity of the disease, often leading to organ failure with associated morbidities, results in a reduced life expectancy, rarely exceeding 50 years [1]. There is no specific treatment for this genetic disease and current management consists of symptomatic therapies.

ALMS is caused by mutations in ALMS1, a large gene located on chromosome 2p13 with ubiquitous expression [2, 3]. The ALMS1 protein localizes to the centrosomes and basal bodies of ciliated cells and may play a role in microtubular organization and cilia assembly or function [3, 4]. In addition, this protein has been implicated in intracellular trafficking, regulation of cilia signalling pathways, and cellular differentiation among others [5]. Pathological observations from post-mortem specimens reveal extensive fibrosis in many organs including the kidney, heart, liver, and lung [6]. Furthermore in vitro dermal fibroblast cultures from ALMS patients display cytoskeleton abnormalities, impaired migration, increased production of collagens, have augmented cell cycle length, and show enhanced resistance to apoptosis [7].

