### Location and setting

Study PBI-4050-ATX-9-05 is sponsored by Prometic Biosciences and subjects are recruited from the clinical service at University Hospitals Birmingham NHS Foundation Trust, United Kingdom (UK), which is a nationally commissioned specialist service for ALMS.

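### The historical comparison contrasts slopes only, so it cannot describe an immediate, sustained change at first dose; a level change should be reported beside the slope change, for named variables

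*Protocol article*

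**What the plan says.** All of the analysis wording is in the protocol article under Sample size and statistical analysis.

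- Efficacy and other before/after variables: "Paired t-test or where appropriate the non-parametric equivalent (Wilcoxon signed-rank test) will be used to compare variables before and after intervention". The null is zero change.
- Safety laboratory values: "Absolute values and changes from baseline in safety laboratory tests will be summarized by visit over time and presented in shift tables".
- The next sentence, introduced as a way to evaluate the shift over time, says that "a mixed model comparing the slope before baseline (historical data) to the slope after baseline (on-treatment data) will be used". It names no variables and no level term, and this is the only mention of historical data.

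The Background says of the disease: "Increasing systemic fibrosis develops as patients age, with clinical manifestations in multiple organs". The design is single-arm. Subjects come from one clinic, "which is a nationally commissioned specialist service for ALMS", which makes earlier routine values plausible, but the article does not say which variables have them.

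**The concern.** Without a control arm, a subject's own earlier course is the only reference for what would have happened untreated. The article limits that reference to one quantity, slope against slope. A drug can act on a laboratory value within weeks and then hold it at the new level. That pattern is a change of level with no change of slope, so the stated contrast either returns nothing or reports a continuing trend that is not there.

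The paired tests do react to a change of level, but they measure it from zero change. Where the untreated course drifts, as the Background says fibrosis does, the paired result mixes drift and drug effect. So the analysis that uses history does not capture a step, and the analysis that captures a step does not use history.

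**Working it through.** The article gives no effect size, SD or power for this comparison, so there is no stated figure to reproduce. The check is of model structure.

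**Inputs from the article (Table 2).** On-treatment visits at Weeks 4, 8, 12, 16, 20 and 24. Extension visits at 12, 24, 36 and 48 weeks, i.e. study Weeks 36, 48, 60 and 72. Week 1 is taken as baseline (time 0).

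**Assumptions.** Historical visits at -104, -78, -52, -26 and 0 weeks. True effect: a step of -10 units after time 0, no slope change, and no drift in this first part.

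**1. Separate lines.** Pre-baseline values are all 0, so the slope is 0. On-treatment values are all -10, so the slope is 0. The slope difference is 0 - 0 = 0 for any step size. The -10 appears only in the difference of levels, which is not the stated contrast.

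**2. Lines joined at baseline.** Model: y = a + b·t + c·max(t, 0), where c is the slope change.

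Least-squares equations with 24 weeks of data:
- 11a - 176b + 84c = -60
- -176a + 21736b + 1456c = -840
- 84a + 1456b + 1456c = -840

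The second minus the third gives b = 260a/20280 = a/78. Solving: a = -4.09, b = -0.052, **c = -0.288 per week**. The true c is 0.

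With 72 weeks of data:
- 15a + 40b + 300c = -100
- 40a + 34120b + 13840c = -3000
- 300a + 13840b + 13840c = -3000

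Again b = a/78. Solving: a = -6.77, b = -0.087, **c = +0.017 per week**. Same step, same history, opposite sign.

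**3. Level term added.** With y = a + b·t + c·max(t, 0) + d·[t > 0], both data sets return d = -10 and c = 0 exactly.

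**4. With noise and drift.** Simulation, 4000 runs per setting. Further assumptions: residual SD 1, untreated drift +0.5 SD per year, step -1.5 SD, two-sided 5% level, 24 weeks of data unless stated, n = 8 / 12 / 18.
- Joined lines, slope test: significant in 54% / 78% / 93%, so a one-off shift is read as a trend. On 72 weeks: 6% to 8%.
- Separate lines, slope test: about 5% at each n.
- Level term: mean estimate -1.5, significant in 85% / 98% / 99.9%.
- Paired Week 24 test: significant in 58% / 80% / 95%, mean change about -1.27. That is -1.5 + 0.5 × 24/52 = -1.5 + 0.23, so the step is seen but shifted by the drift.

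**5. Paired test against zero in a progressive disease.** Noncentral t with noncentrality δ√n, where δ is the true mean change in SDs of the change score (assumed).
- Drug fully halts progression: δ = 0, so benefit is declared in 2.5% at any n.
- Drug halves a 1 SD progression: δ = 0.5, so significant worsening is declared in 23% / 35% / 52% for n = 8 / 12 / 18.

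**The case against.** The strongest reply is that an immediate change does not go unnoticed. The sentence before the slope model provides absolute values and changes by visit, and shift tables. Paired tests are planned. Clinically significant laboratory changes are recorded as adverse events, there is a transaminase discontinuation criterion, and a Data Safety Monitoring Board reviews individual safety data. All of this stands. A reader might infer that a prompt laboratory safety signal would be missed, and the article does not support that.

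Second, the article names a contrast, not a full set of model terms. If separate lines are fitted, a level difference is already in the model, and an analysis plan that is not shown may report it. This stands in part: under that reading the change is one of reporting. But the article does fix the quantity to be compared, and that quantity is the slope.

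Third, the restriction to safety laboratory tests is inferred from sentence order. That is correct, and the safety biochemistry already includes liver enzymes and lipids. It supports naming the variables, not a claim that efficacy-relevant variables are wholly excluded.

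Fourth, the study is exploratory and openly single-arm, and no historical elastography, MRI, biopsy or clamp values are documented. So a better historical model cannot repair the zero-change null for those measures. That also stands. The article nevertheless sets a 0.05 significance level and says that therapeutic efficacy will be assessed over 24 weeks, so the meaning of the paired results should be stated.

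**Conclusion.** The point holds as a cheap improvement. The stated contrast cannot describe an immediate, sustained change. The slope difference is exactly 0 with separate lines, which needs no assumption beyond a pure step. With joined lines the step is misattributed to slope: -0.29 per week on 24 weeks and about +0.02 per week on 72 weeks for a -10 step. Those two figures are illustrations that rest on the assumed history. It would be wrong to carry the 24-week line forward as the predicted error at Week 72, because the scheduled extension visits change the fit and reverse the sign.

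The loss is a valid comparison with the subject's own prior trend, not safety detection. The paired-test percentages show the direction of the problem under assumed drift. The article gives no drift rate, so they are not a forecast for any endpoint.

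**What to change.** - State that the historical-versus-on-treatment mixed model includes both a level change and a slope change at first dose, and report both with 95% CIs.
- Name the variables that the model covers.
- Apply it as supportive analysis to secondary efficacy variables for which pre-baseline values exist, for example HbA1c, as well as the lipids and liver enzymes already in the safety panel.
- State that paired tests, including those on fibrosis measures without historical values, estimate uncontrolled change from baseline in a progressive disease, not drug effect.

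Cost: analysis wording, at most one added model term, and some extraction of records. No new visits or procedures are needed. Downside: historical clinic values will be irregular, and estimating level and slope together gives wider intervals.

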#### Assessment of adipose tissue

Adipose tissue samples will be used to quantify the effects of PBI-4050 on fibrosis in adipocytes. Subcutaneous adipose tissue from ALMS subjects is to be characterised using histo-morphometry and immunohistochemistry staining. The biopsies are collected from the abdomen on the lateral side of the umbilicus on the abdominal wall. After administration of local anaesthetic (1% lignocaine), a 1-cm subcutaneous incision is made with a scalpel and the removed sample of adipose tissue is immediately preserved in 2 parts in formalin and RNAlater® Stabilization Solution (Thermofisher scientific). The samples stored in formalin are then embedded in paraffin to make formalin-fixed paraffin-embedded (FFPE) blocks. The FFPE blocks are cut and stained with haematoxylin and eosin and picrosirius-red staining for quantification of adipose tissue fibrosis. Adipocyte size is measured by means of light microscopy. Immunohistochemistry with macrophage, T-cell and collagen markers will be performed to quantify inflammatory activity and collagen deposition. Global gene expression in adipocytes will be measured. Adipose tissue stored in RNAlater is prepared using RNeasy Lipid Tissue (QIAGEN) and next generation gene sequencing performed to access expression of pro-fibrotic genes.

Adipose tissue microdialysis is used to sample interstitial fluid intermediary metabolites in the form of glycerol, glucose, pyruvate and lactate, which act as a marker of adipose tissue lipolysis. A microdialysis catheter (CMA microdialysis [CMA 106/107], Sweden) is inserted approximately 10 cm lateral to and at the level of the umbilicus via a subcutaneous incision after local anaesthetic (1% lignocaine). Samples are collected every 30 min into micro-vials (0.3 μL/min) until the end of the hyperinsulinaemic-euglycaemic glucose clamp.

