### Discontinuation or withdrawal of study subjects

PBI-4050 will be permanently discontinued for the following reasons:Subject’s withdrawal of consent;An AE, which in the opinion of the investigator warrants discontinuation of treatment;Pregnancy;Death;Substantial protocol deviation;Investigator’s decision;Sponsor’s decision;Subject starting a prohibited therapy (see Section 5.6);aspartate transaminase or alanine transaminase rises to > 5 × upper limit of normal;A drop in heart rate from baseline by 15 beats per minute that is associated with clinically relevant cardiovascular symptoms as determined by the investigator;A drop in systolic blood pressure by 20 mmHg or diastolic blood pressure by 15 mmHg from baseline that is associated with clinically relevant cardiovascular symptoms as determined by the investigator.

Subjects who discontinue study treatment but have not withdrawn consent will be asked to attend the appropriate End-of-Treatment and End-of-Study visits, depending upon whether they withdraw before or after Week 24. Subjects who withdraw consent will not have further study-related information collected for the clinical trial database, with the exception of follow-up on on-going AEs or any new AEs within the safety follow-up period. Subjects who withdraw due to AEs will be followed until the event has resolved or stabilized.

In the case of any substantial deviation from the protocol, the investigator and sponsor will decide on the further participation of the subject in this study, having discussed all relevant aspects. The sponsor may discontinue the study in its entirety before its completion for reasonable cause, provided that written notice to the investigator, regulatory authorities and independent ethics committee (EC) is submitted in reasonable time in advance of the intended termination.

If subjects decide to enter the ALMS rollover study (Study PBI-4050-CT-9-10) after completing the 36- or 48-week extension period, then they will sign an informed consent for that study and stop participation in the current study.

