### Trial status

Recruitment to Study PBI-4050-ATX-9-05 began in February 2016. The study has recruited 12 subjects in the main study and 9 subjects in the extension phase. The study is currently recruiting in the UK and scheduled to end in 2018.

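### Repeated-measures ANOVA on observed data without imputation loses a subject from the microdialysis comparison when one vial is missing; a linear mixed model would keep that subject

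*Protocol article*

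**What the plan says.** All of the relevant wording is in the section on sample size and statistical analysis of the protocol article. Where a test yields several time points, "where there are multiple time points during the same test, repeated measures analysis of variance will be used"; adipose tissue microdialysis is the example given. The same section then states: "All statistical analyses will be made using observed data. No imputation will be made". SPSS is named for all analyses. A mixed model is already planned there, but only to compare slopes before and after baseline.

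The section on adipose tissue sets the sampling: "Samples are collected every 30 min into micro-vials", continuing to the end of the glucose clamp. The section on insulin secretion and resistance describes a 4-hour procedure. Table 2 places the clamp and microdialysis at Week 1 and Week 24.

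For two-point comparisons the plan is different: a paired t-test or Wilcoxon signed-rank test "will be used to compare variables before and after intervention".

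**The concern.** Classical repeated-measures ANOVA treats a subject's samples as one row and uses only full rows. The article does not mention listwise deletion, but it follows from that method combined with no imputation. A subject with 15 good vials out of 16 would contribute nothing to the comparison of the two tests. Microdialysis is the most exposed assessment because it collects many small samples from each subject. With at most 18 subjects in a very rare disease, discarding usable samples is costly. What is at stake is the precision of the microdialysis result, and of any other serial-sample comparison analysed in this way.

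**Working it through.** **The plan's own figures.** The article enrols 18 subjects and deems at least 8 necessary. It gives no effect size, standard deviation, power or dropout rate, so neither number can be reproduced. Here 8 serves only as a yardstick; the article does not tie it to the microdialysis analysis.

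**Inputs from the article.** Sampling interval 30 min; procedure length 4 h; two tests; 18 subjects planned; 12 recruited to the main study at the time of writing.

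**Assumptions.** Collection spans the full 4 h. Each vial is lost independently with probability m. The article gives no value for m, so a range is shown.

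**Step 1: vials per subject.** 240 / 30 = 8 per test; 2 × 8 = 16 over both tests.

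**Step 2: expected complete subjects.** The chance of a complete profile of k vials is (1 − m)^k, and the expected number of complete subjects is N(1 − m)^k.

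| m (assumed) | (1 − m)^16 | Complete of 18, both tests | Complete of 12, both tests | (1 − m)^8 | Complete of 18, one test alone |
|---|---|---|---|---|---|
| 1% | 0.851 | 15.3 | 10.2 | 0.923 | 16.6 |
| 2% | 0.724 | 13.0 | 8.7 | 0.851 | 15.3 |
| 5% | 0.440 | 7.9 | 5.3 | 0.663 | 11.9 |
| 10% | 0.185 | 3.3 | 2.2 | 0.430 | 7.7 |

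For example, 18 × 0.95^16 = 18 × 0.440 = 7.9. At that rate the binomial chance of fewer than 8 complete subjects out of 18 is 0.425. A mixed model would use 95% of the samples.

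**Step 3: precision.** The 95% confidence half-width for a mean change, in units of the SD of the change, is t(0.975, n − 1)/√n.
- n = 18: 2.110/4.243 = 0.50
- n = 13 (2% loss): 2.179/3.606 = 0.60
- n = 8 (about 5% loss): 2.365/2.828 = 0.84

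**Step 4: what a mixed model recovers.** A small simulation (200 runs per setting) used two tests of 8 samples, between-subject SD 1, subject-by-visit SD 0.5, residual SD 0.6, a shift of 0.6 and vials missing completely at random. All these values are assumptions. The mixed model had random subject and subject-by-visit effects and independent residuals.

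| Setting | Power, ANOVA on complete subjects | Power, mixed model | Power, no data missing |
|---|---|---|---|
| N = 18, 2% missing | 0.735 | 0.915 | 0.92 |
| N = 18, 5% missing | 0.51 | 0.90 | 0.905 |
| N = 12, 5% missing | 0.31 | 0.73 | 0.73 |

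At N = 18 and 5% missing, the SD of the estimated shift fell from 0.26 to 0.17. With no true shift, the mixed model rejected in 1.5% of runs, the complete-data test in 1.5% and the ANOVA on complete subjects in 7%. With 200 runs these null rates are too imprecise to establish the error rate of any of the methods.

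**The case against.** The strongest reply is that the loss rests on inputs the article does not contain. That stands. If losses cluster, as when one catheter fails, the same overall rate leaves more subjects complete. The ANOVA wording also refers to time points within the same test, so a reader may count 8 vials and not 16; the one-test column covers that reading. At 1% loss the effect is small. Microdialysis serves an exploratory objective, the primary objective is safety, and no decision rests on this test. A mixed model with several variance components is also demanding with 8 to 18 subjects. These replies limit the size and weight of the point. They do not change the fact that the stated method discards incomplete profiles.

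A reader might infer stronger criticisms that the article does not support:

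- **That the paired tests share the fault.** A paired test loses only the affected pair: at 5% missing per visit, 18 × 0.95² = 16.2 pairs remain. The article plans these tests before and after intervention, not at each of the 11 visits at which biomarkers are scheduled. A mixed model adds little to a two-point comparison.
- **That selection into the extension biases the result.** The extension is elective and follows Week 24, so entry to it does not affect a Week 24 versus baseline comparison. The trial status section states that "The study has recruited 12 subjects in the main study and 9 subjects in the extension phase", but recruitment was continuing, so 9 against 12 is not an attrition figure.
- **That the type I error is inflated through lack of sphericity.** This would apply to an uncorrected F test. The article does not say the test will be uncorrected, and a condensed article may leave a named correction to the full protocol or analysis plan.

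**Conclusion.** The point holds for the serial within-test samples. The article fixes a method that, with no imputation, loses a subject from the comparison for one missing vial. Over both tests, the expected loss from 18 subjects is 18 − 15.3 = 2.7 at 1% vial loss, 18 − 13.0 = 5.0 at 2% and 18 − 7.9 = 10.1 at 5%. If each test is analysed alone, it is 1.4, 2.7 and 6.1. These figures rest on an assumed, independent loss rate, on collection over the full 4 hours, and on reading the method as classical repeated-measures ANOVA. The consequence is avoidable imprecision in an exploratory analysis. The point does not touch the safety objective or the before/after paired tests. The change is worth making because it is cheap, but nothing confirmatory depends on it.

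**What to change.** For microdialysis and any other comparison of serial samples within a test, replace repeated-measures ANOVA with a linear mixed model fitted to all observed samples in the software already named. Specify:

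- fixed effects of visit, time within test, and visit-by-time;
- random subject and subject-by-visit effects;
- one simple residual structure chosen in advance, with a stated simpler fallback if the model does not converge;
- Satterthwaite or Kenward-Roger degrees of freedom.

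The rule against imputation can stand, since the model uses incomplete profiles directly. Leave the two-point paired tests unchanged.

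The cost is a change of wording and of procedure; no new data are needed. A covariance structure has to be prespecified, with few subjects to support it. The model is valid only if vials are missing at random, so it would not repair losses that depend on the unobserved values. It also recovers less where a subject lacks a whole test than where single vials are missing.

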### Study objectives

The primary objective is to evaluate the safety and tolerability of 800 mg PBI-4050 (Investigational Medicinal Product [IMP]), administered orally once daily.

The secondary objectives are:To evaluate the effect of the IMP on metabolic syndrome parametersTo evaluate the effect of the IMP on pro-inflammatory/inflammatory, fibrotic, diabetic, and obesity biomarkers in blood and urineTo evaluate the effect of the IMP on antidiabetic treatment, including oral therapy and insulin requirements

The exploratory objectives are:To examine the effect of the IMP on the histological appearances of fat biopsies, in particular the degree of fibrosis and macrophage infiltration;To analyse the effect of the IMP on the global metabolome using systemic blood and adipose tissue-specific microdialysis samples;To analyse the effect of the IMP on the microdialysate fractions using adipose tissue microdialysis samples;To assess the effect of the IMP on liver stiffness using transient elastography;To measure the effect of the IMP on the fat content and fibrosis burden in the liver using MRI;To measure the effect of the IMP on cardiac fibrosis and function using MRI and on biomarkers, including N-terminal pro-brain natriuretic peptide (NT-pro-BNP);To evaluate the effect of the IMP on additional pro-inflammatory/inflammatory, fibrotic, diabetic, and obesity biomarkers in blood and urine;To evaluate the effect of the IMP on glucose, insulin, and lipid dynamics using the hyperinsulinaemic-euglycaemic clamp test.

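### Single-variable paired tests in SPSS are fixed for all analysis, with no exception for adipose sequencing or the blood metabolome; under false discovery rate control this costs material power at 8 to 12 pairs, but little at 18

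*Protocol article*

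**What the plan says.** All the analysis rules stand in the article's section on sample size and statistical analysis.

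- Before-after rule: "Paired t-test or where appropriate the non-parametric equivalent (Wilcoxon signed-rank test) will be used to compare variables before and after intervention".
- Switch between the two tests: "In the event that the normality assumption fails at the 0.10 alpha level of significance, the Wilcoxon Signed-Rank test will be used instead".
- Repeated samples within one test have their own rule: "for example adipose tissue microdialysis where there are multiple time points during the same test, repeated measures analysis of variance will be used".
- Software: "All analysis will be conducted using SPSS statistical software". The significance level is p<0.05, and no FDR threshold is given.

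Two endpoints have many features. The section on adipose tissue says "Global gene expression in adipocytes will be measured", and gives as the purpose of the sequencing "next generation gene sequencing performed to access expression of pro-fibrotic genes". The exploratory objectives include "To analyse the effect of the IMP on the global metabolome using systemic blood and adipose tissue-specific microdialysis samples".

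Table 2 places the biopsy at week 1 and week 24 only, so each subject gives one pair. The article names a minimum of 8 subjects, a planned total of 18, and 12 recruited to the main study at publication.

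**The concern.** The before-after rule covers variables without exception, and the software sentence covers all analysis. Read plainly, each gene and each blood metabolite would get its own paired t-test or Wilcoxon test.

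That is a valid test but an inefficient one. With n pairs, each feature's variance rests on n-1 degrees of freedom: 7, 11 or 17 at 8, 12 or 18 pairs. A moderated paired test, or a paired count model with shared dispersion, also uses what the other features show about variance. The Wilcoxon branch has a further limit, because its smallest possible p-value is fixed by n.

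At stake is how much a small set of invasive biopsies, in a very rare disease, can show about changes in gene expression.

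**Working it through.** **The plan's own figure.** There is none to reproduce. The article gives no power, effect size or standard deviation (SD), and no derivation of 8 or 18. Everything below except the Wilcoxon limit rests on assumed inputs.

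**Why sharing variance helps, and when.** Let s² be a feature's own variance of paired differences, s0² the typical variance across features, and d0 the prior degrees of freedom.

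- Ordinary: t = mean × √n / s, with n-1 df.
- Moderated: t = mean × √n / √[(d0·s0² + (n-1)·s²)/(d0+n-1)], with n-1+d0 df.

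With d0 = 4 the df rise from 7 to 11 at n=8 and from 17 to 21 at n=18. The two-sided critical value at p=0.001 falls from 5.41 to 4.44 at n=8, but only from 3.97 to 3.82 at n=18. At p=0.05 and n=8 it falls only from 2.36 to 2.20. So the gain should be largest with few pairs and a strict threshold.

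**Simulation 1: the stated rule against a moderated paired t-test.** Assumed: 10,000 independent features, typical SD of paired difference 0.5 log2 units, d0 = 4, Benjamini-Hochberg 5% FDR. Settings: (A) 2% of features changed by 0.8 log2 units; (B) 5% by 0.6; (C) 10% by 0.8. Share of true changes found, stated rule against moderated:

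| Pairs | A | B | C |
|---|---|---|---|
| 8 | 13% vs 34% | 5% vs 6% | 39% vs 66% |
| 12 | 56% vs 70% | 44% vs 53% | 75% vs 83% |

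At 18 pairs the gain is 3 to 6 points. In B at 8 pairs neither method finds much.

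**Simulation 2: ordinary against moderated paired t-test, other assumptions.** 20,000 features, 5% changed by d of each feature's own SD, d0 from 4 to 10, 5% FDR:

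| Pairs | d | Ordinary | Moderated |
|---|---|---|---|
| 8 | 1.0 | 0.00 | 0.02-0.08 |
| 8 | 1.5 | 0.20-0.21 | 0.54-0.71 |
| 12 | 1.0 | 0.19-0.20 | 0.30-0.40 |
| 12 | 1.5 | 0.85 | 0.91-0.95 |
| 18 | 1.0 | 0.70-0.71 | 0.75-0.78 |
| 18 | 1.5 | 0.99 | 1.00 |

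**Small panel.** With 100 genes and 20% changed, the stated rule found 25-54% against 43-76% at 8 pairs, and 61-81% against 69-87% at 12.

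**At the stated p<0.05, unadjusted.** The gain is about 5 to 9 points at 8 pairs and 2 to 3 at 12. For d=1.0, power goes from 0.68 to 0.73-0.76 at 8 pairs and from 0.88 to 0.90-0.91 at 12; at 18 it moves by less than one point. That threshold would give 10,000 × 0.05 = 500 false positives among 10,000 unchanged features.

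**Wilcoxon limit (exact).** The smallest two-sided p is 2/2^n: 2/256 = 0.0078 at n=8, 2/4,096 = 0.00049 at n=12, and 2/262,144 = 0.0000076 at n=18. Under Benjamini-Hochberg at 5% with m features, a feature at that floor can pass only if at least floor × m / 0.05 features are declared together, t-tested ones included. For m = 10,000 this is 0.0078125 × 10,000 / 0.05 = 1,562.5, so 1,563 features at n=8; at n=12 it is 98. In setting C only 1,000 features are truly changed, so at n=8 a feature routed to Wilcoxon has practically no chance. About 10% of features are routed there even when the differences are normal.

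**The case against.** The strongest reply is that the article never assigns a test to the sequencing or the metabolome. A journal article commonly leaves the pipeline for such data to an analysis plan, which is not shown here. This stands in part: the data fall under the rule only through its general wording. But the article does more than stay silent. It fixes SPSS for all analysis and one pair of tests for before-after variables, so a different method in a later plan would contradict it.

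Several stronger readings are tempting, and the document does not support them.

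- *All metabolome data go to the t-test or Wilcoxon.* Microdialysis with several time points goes to repeated measures analysis of variance. Only the sequencing and the blood metabolome remain under the before-after rule.
- *Thousands of genes will certainly be tested.* Global expression is measured, but the stated use is pro-fibrotic genes, and no feature count is given. The gain does persist in a 100-gene panel.
- *Much of the power is lost anywhere from 8 to 18 pairs, or at any error rate.* The gain is small at 18 and small at unadjusted p<0.05, the only threshold stated.
- *Nothing can be found at 8 pairs.* The floor binds only features routed to Wilcoxon; t-tested features have none.
- *Raw counts will be tested without normalisation.* Nothing says so.

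Two further points stand. The simulations assume independent features and draw variances from the kind of model that the moderated test uses, which favours it somewhat. The study also calls itself purely exploratory, and stored sequencing data can be reanalysed.

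**Conclusion.** The point holds in limited form. The article's wording places adipose sequencing and blood metabolites under feature-by-feature tests in SPSS. Once FDR is controlled, this loses material power at 8 to 12 pairs. In Simulation 1 the gap was 21 and 27 points in two of three settings at 8 pairs (about 1 in the third) and 8 to 14 at 12. These sizes depend on assumed feature counts, effects and variance spread; only the Wilcoxon floor is free of such assumptions. The range of 8 to 12 is realistic, given the stated minimum and the number recruited at publication. If all 18 planned subjects give complete pairs, little is lost. Severity is low: the objectives concerned are exploratory, the tests named are valid, and the issue is efficiency.

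**What to change.** 1. Limit the t-test, Wilcoxon and SPSS sentences to single-variable endpoints. Leave the repeated measures rule for microdialysis time series as it stands.
2. Analyse the sequencing on depth-normalised counts, with subject as the pairing factor and visit as the effect, in a model that shares variance across genes (moderated linear or negative-binomial).
3. Use a moderated paired test on log-scale blood metabolite values.
4. State that both are reported under FDR control and run in suitable scripted software, with the code archived.

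The cost is a few sentences, freely available software and a second documented analysis outside SPSS. It needs no extra subjects, samples or visits.
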